**Methods:**

The research implements a prospective randomized controlled trial (Project Swerve) of 600 YMSM and transgender people recruited both online and in person. Eligibility criteria include participants who (1) are between the ages of 15 to 29 years, (2) live in the Detroit Metro Area, (3) self-identify as a man or transgender man or woman, (4) have had sexual contact with a man in the 6 months before enrollment, (5) self-report binge drinking or any substance use in the 3 months before enrollment, and (6) self-report an unknown or negative HIV status upon enrollment. Participants are randomized to receive, 3-months apart starting at baseline, 2 individual sessions. Sessions are CTR-only, SUBI-only, CTR followed by SUBI, or SUBI followed by CTR.

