### Trial Design

The research activities involve a 4-arm factorial RCT of approximately 600 AOD-using YMSMTG aged 15-29 years in the DMA. We will follow participants for 18 months, with follow-up assessments collected every 3 months.

The intervention comprises 2 visits separated by 3 months. Participants are randomized to receive either CTR (control) or a SUBI-adapted version of CTR (referred to as SUBI; intervention) in each visit. To examine how the sequencing and dosing of interventions impacts efficacy, we randomize at baseline into a factorial RCT. The control arm will receive CTR-only at both study visits 1 and 2. Experimental arm 1 (CTR+SUBI) will receive CTR at visit 1 and SUBI at visit 2. Experimental arm 2 (SUBI+CTR) will receive SUBI at visit 1 and CTR at visit 2. Experimental arm 3 (SUBI+SUBI) will receive the intervention condition at visits 1 and 2. Individuals who test HIV-positive at study visits 1 or 2 will receive case management and linkage to care, as offered routinely by each ASO where study activities take place.

This 4-arm factorial randomized design will help answer 3 important questions: (1) what is the impact of adapting current CTR to include SUBI on HIV engagement in care and sexual- and substance-related risk-taking behaviors among high-risk YMSMTG; (2) what combination of services (CTR-only, CTR+SUBI, SUBI+CTR, SUBI+SUBI) has the greatest impact on engagement in HIV prevention (where engagement in care is defined as routine HIV testing for seronegative YMSMTG and linkage and retention in care for seropositive YMSMTG); and (3) if effective, what are the costs of delivering SUBI compared with those of delivering CTR?

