### Sample Size and Power

The primary outcome for the proposed trial is successful engagement in care. For those who test seronegative at baseline, we define engagement in care as participation in routine HIV testing. For those who test seropositive at baseline, we define engagement in HIV care as linkage and retention in HIV care (per the Institute of Medicine guidelines of linkage within 30 days of diagnosis and at least 2 physician visits with a CD4 and viral load test in 12 months) and achievement of viral suppression. We define power as correctly identifying the difference in the proportions of YMSM with serospecific engagement in HIV care within 15 months of each active treatment condition (3 arms: SUBI-CTR, SUBI-SUBI, CTR-SUBI) to the control arm (CTR-CTR), thus powering for 3 independent hypothesis tests. Our sample size calculations are based on a 2-sample test of proportions using a 2-sided significance level of *P*<.05 altered by the number of comparisons using a Bonferroni adjustment (significance level is *P*=.02 for 3 comparisons). To have 80% power to compare each active treatment to the control group in a 4-arm trial, we require at least 500 participants to find a 20% difference between each treatment and control and 228 participants to find a 30% difference. To allow for 20% loss to follow-up (our previous trials have each achieved retention rates of >90%), we estimate a sample of 600 YMSMTG to be enrolled.

Participants may continue the study even if they miss follow-ups or visits intermittently over the data collection period. We will compare those who completed different follow-up interviews with those who did not on key predictors from the baseline assessment to check for possible sampling bias due to missing data. Missing data will be minimized by the computer-based entry for all measures. The use of Expectation-Maximization algorithm and multiple imputation approach in longitudinal analyses will help overcome missing data concerns when appropriate.

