### Statistical Analysis

Descriptive statistics of the clinical and demographic characteristics of the participants will described for all and by treatment group. These will be compared between treatment groups using *t* tests or Wilcoxon rank sum tests for continuous variables and chi-square tests for categorical variables. We will conduct primary analyses of our pooled successful engagement measure using logistic regression analyses to compare each active treatment group with the control in pairwise comparison tests at an adjusted significance level of .017 to reduce Type-I errors in our 4-arm trial. We will then conduct exploratory logistic regression analyses by sero-status. For seronegative YMSMTG, the proportion of participants who obtain at least 2 tests at least 3 months apart within 15 months will be calculated and presented with corresponding 95% exact binomial CIs. Among seropositive YMSMTG, we will examine how intervention conditions influence HIV linkage and retention in care per IOM guidelines. We will also examine for all participants the pursuit of substance use treatment services (if necessary). Hence, for seronegative participants, the outcome will be repeat HIV testing at regular intervals, and for seropositive participants, the outcome will be linkage and retention in care. We will not consider viral suppression in the regression analysis due to the short time period available to achieve suppression. However, we will present descriptive statistics on viral load and suppression across the 4 treatment arms. The regression will be run with group assignment in the model while controlling for patient, structural, and agency characteristics. Interactions between group assignment and these characteristics will be tested to explore potential moderators of treatment effect. We will repeat these analyses for STI/ATOD biomarkers conducted during the trial. Additional analyses include comparing groups in (1) the average number of tests obtained using Poisson regression and (2) time to getting tested using repeated events survival analysis.

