## Results

Project Swerve launched in April 2017 and is currently recruiting YMSMTG into the trial. Current recruitment strategies combine online and in-person (venue-based sampling) approaches. As of February 22, 2018, 5183 people began the screener survey, of which 3178 (61.32%) completed it. In total, 594 (18.70%), people successfully screened were eligible to participate in the study, of which 378 (63.6%) provided consent and 223 of these (58.9%) enrolled into the study. Of these, 160 (71.7%) have completed the baseline survey and 18 dropped from the study; the remaining 142 participants have been randomized into study arms as follows: 36 SUBI-SUBI; 36 SUBI-CTR; 34 CTR-SUBI; and 36 CTR-CTR.

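### The target of 600 is stated as a number enrolled, but the trial's own count puts enrolment before randomization; the unit should be fixed as a number randomized and the power restated

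*Protocol article*

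**What the plan says.** Sample Size and Power gives the requirement for 80% power: "we require at least 500 participants to find a 20% difference between each treatment and control and 228 participants to find a 30% difference". It then allows for 20% loss to follow-up and concludes: "we estimate a sample of 600 YMSMTG to be enrolled". It mentions no other loss.

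Two other places attach the same number to the randomized trial. Trial Design says: "The research activities involve a 4-arm factorial RCT of approximately 600 AOD-using YMSMTG aged 15-29 years in the DMA". The abstract says: "The research implements a prospective randomized controlled trial (Project Swerve) of 600 YMSM and transgender people recruited both online and in person".

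The Results section is the only place where people are counted stage by stage, as of February 22, 2018, with recruitment open. Of 378 who consented, "223 of these (58.9%) enrolled into the study". Of the 223, 160 had completed the baseline survey and 18 had dropped out, and "the remaining 142 participants have been randomized into study arms as follows" (36, 36, 34 and 36).

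**The concern.** Power depends on how many people are randomized and then analysed. A 20% allowance for loss to follow-up covers people who leave after entering the comparison. It does not cover people who enrol and never reach allocation.

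In Results, 160 − 18 = 142, so the 18 dropouts left before allocation, and enrolment is a stage earlier than randomization. The Screening section fits this order, since the online survey is completed before the first visit. The same 600 is thus an enrolment figure in one section and the size of a randomized trial in two others, although the trial's own count shows that these stages differ.

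If recruitment were tracked to 600 in the Results sense, losses before randomization would come on top of the 20%, and the three pairwise primary comparisons would rest on fewer people than the calculation assumes.

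**Working it through.** **Inputs from the article.** 500 participants for a 20-point difference and 228 for 30 points; 80% power; four equal arms; 20% loss; 223 enrolled, 160 surveyed, 18 dropped, 142 randomized. The significance level is rounded in Sample Size and Power ("significance level is *P*=.02 for 3 comparisons") and given more exactly in Statistical Analysis ("pairwise comparison tests at an adjusted significance level of .017"). I use .05/3, two-sided, so z = 2.394.

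**Assumption.** The control-arm rate is not given. I take 30%, because it reproduces both of the plan's figures, and vary it below.

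**Step 1: reproduce the plan's figures.** Two-sample test of proportions with pooled variance and no continuity correction:

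n per arm = [z(α/2)·√(2p̄(1−p̄)) + z(β)·√(p1(1−p1) + p2(1−p2))]² / (p2−p1)²

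- 30% vs 50%: (2.394 × 0.6928 + 0.8416 × 0.6782)² / 0.04 = 124.3, so 125 per arm and **500** in total.
- 30% vs 60%: (2.394 × 0.7036 + 0.8416 × 0.6708)² / 0.09 = 56.2, so 57 per arm and **228** in total.

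Both match. At .02, 40% vs 60% also gives 500, but no control rate checked brings the 30-point case above 220.

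The figure 600 equals 500 × 1.2. To keep 500 after losing 20%, the number is 500/0.8 = **625**; 600 × 0.8 = 480.

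**Step 2: what 600 enrolled would yield, counted as in Results.** Of the 223 enrolled, 81 were not randomized: 18 dropouts and 63 without a completed baseline survey. The article does not call those 63 lost, so three cases are needed.

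- A: only the 18 known dropouts are lost. 205/223 = 91.9%.
- B: all 63 complete the survey and then drop at the observed rate. 142/160 = 88.8%.
- C: the snapshot ratio is final. 142/223 = 63.7%.

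Power = Φ{[(p2−p1)·√n − z(α/2)·√(2p̄(1−p̄))] / √(p1(1−p1) + p2(1−p2))}, with n per arm after 20% loss. For case B with 30% vs 50%: (0.2 × √106.5 − 2.394 × 0.6928) / 0.6782 = 0.598, and Φ = 72.5%.

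| Case | Randomized | Analysed | Per arm | 30 vs 50 | 40 vs 60 | 20 vs 40 | 35 vs 65 |
|---|---|---|---|---|---|---|---|
| Plan's requirement | – | 500 | 125 | 80.3% | 78.4% | 86.0% | 99.3% |
| 600 randomized | 600 | 480 | 120 | 78.4% | 76.4% | 84.4% | 99.1% |
| A | 552 | 441 | 110.3 | 74.3% | 72.2% | 80.7% | 98.5% |
| B | 532 | 426 | 106.5 | 72.5% | 70.4% | 79.1% | 98.1% |
| C | 382 | 306 | 76.4 | 55.3% | 53.2% | 62.2% | 91.6% |

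**Step 3: separate the two causes.** From 500 to 480 (80.3% to 78.4%) is the inflation arithmetic. From 480 to 441 or 426 (78.4% to 74.3% or 72.5%, so 4 to 6 points) is the unit of the target.

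**Step 4: a milder retention assumption.** With 90% retention, close to what the article reports for earlier trials, case A leaves 551.6 × 0.9 = 496, almost the required 500.

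**The case against.** The strongest reply is that *enrolled* in the sample-size paragraph simply means entered into the randomized comparison. The 600 is the number from which follow-up loss is taken, and such loss is normally counted among people already allocated. Read that way, the sample-size paragraph, Trial Design and the abstract agree, and only the progress report uses the word differently. This is plausible and the article does not exclude it. It does not remove the point, because no sentence says that 600 will be randomized, and the only operational count uses the same word for an earlier stage.

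A reader might also infer more than the article supports:

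- **That about 36% of enrollees are lost before randomization, so 600 enrolled means 382 randomized and 55% power.** The count is a snapshot of open recruitment. Only 18 people are reported as dropped; the other 63 may still be in process.
- **That every primary comparison falls well below 80% power.** This concerns the 20-point difference only. The 30-point difference keeps more than 90% in every case, and case A with 90% retention is nearly at target.
- **That the plan closes recruitment at 600 enrolled.** No closing rule is stated, and a journal article may leave recruitment tracking to the full protocol.
- **That replacing one word cures the problem.** It does not: 600 randomized with 20% loss still leaves 480.

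**Conclusion.** The point holds as an inconsistent unit with a conditional cost. The article gives 600 as an enrolment target, describes a randomized trial of that size, and counts enrolment before randomization.

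If 600 is counted as in Results, the planned 20% loss leaves fewer than 500 in all three cases. That shortfall in numbers does not depend on the control rate. The power does. For 30% vs 50% it is about 73% to 74% if most pending enrollees go on, of which 4 to 6 points come from the unit and about 2 from the inflation arithmetic. At a 40% control rate it is 70% to 72%. At 20% it is 79% to 81%, but that rate does not reproduce the plan's 500. The 55% figure is a lower bound that would require the interim ratio to be final, which is not shown.

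If 600 means randomized, the unit problem disappears and about 78% power remains at 20% loss. The correction is worth making, but a large loss of power is not established.

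**What to change.** In Sample Size and Power, state the target as a number randomized, track recruitment on that count, and apply the 20% loss from randomization. Then restate the result:

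- keep 600 randomized and report 480 expected for analysis, with about 78% power for 30% vs 50%; or
- keep 500 for analysis and set the target at 625 randomized.

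If 600 is meant as an enrolment target, say so, and give the expected number randomized and its power. For orientation, 625 randomized would need about 680 enrolled (case A) or 704 (case B), and 982 only if the snapshot ratio were final. Report losses before randomization separately from loss to follow-up, and use *enrolled* for one stage only.

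The cost is small. The text change is short, and with 142 randomized at the count date the tracking number could still be set. The downside is a slightly less favourable stated power, or 25 more participants to randomize if 80% is to be kept.

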### Outcomes

The trial focuses on 3 sets of outcomes: engagement in HIV prevention and care services; AOD use; and sexual risk. The trial will also measure satisfaction with the intervention.

#### Engagement in HIV Prevention and Care Services

We will ask YMSMTG having unknown or negative HIV status to indicate the date of any recent HIV and STI tests. At baseline, we will ask participants to note if they have ever been medically diagnosed as having one or more STIs. Among those diagnosed, we will ask if the STI diagnosis occurred in the prior 12 months. In follow-up surveys, we will ask participants to report if they tested for STIs in the prior 3 months and whether any of their tests were reactive.

At each follow-up session (visits 3-7), we will measure the primary outcome of repeat HIV testing. For anyone who tested in each intersurvey period, we will assess the test result and motivations for testing (exposure-related vs regular health checking). For seropositives, the survey will assess the incidence of HIV-related physician visits, including whether CD4 counts and viral load tests were conducted and prescriptions for antiretroviral therapy (ART) were given. We will also ask participants to self-report their adherence to ART using an abbreviated 6-item questionnaire based on the AIDS Clinical Trial Group assessment. Participants are asked to note, using a scale ranging from “never” to “often,” if they missed their HIV medication over the past month for one of the listed reasons. Seropositives will also provide a blood sample for a viral load test. Viral load testing will be done every 6 months. We prioritize viral load tests over a biomarker of adherence, given that adherence is the primary pathway to viral suppression.

#### Biomarkers for HIV Prevention and Care

In addition to self-reported behavioral measures, the study will also collect biomarkers to test for HIV and STIs. At the intervention visits, HIV testing will be performed as part of CTR. STI screening: For syphilis screening, participants will undergo a blood draw for subsequent unheated serum regain test and, for chlamydia and gonorrhea screening, participants will provide a urine sample and pharyngeal, rectal, and/or vaginal swab cultures. Hepatitis C will be assessed using the OraQuick rapid test. Although we expect prevalence of hepatitis C to be low in an AOD population that has low levels of injection drug use (and thus hepatitis C will not be a secondary outcome), we will include hepatitis C testing to assess prevalence in this population. Those who are asymptomatic and test positive will be referred by study staff to local health care providers for further evaluation and treatment. All other STI tests will be processed by the Michigan Department of Health and Human Services. As required by state law, all new positive STI results will be reported to the State Health Department for the purposes of disease surveillance. The requirement for reporting of confidential test results to the health department will be explained in the informed consent. Condoms and water-based lubricant will be provided to all participants. We will screen for STIs at the final study assessment.

#### Alcohol and Other Drugs Use, Misuse, and Consequences

We use the ASSIST [49] to assess frequency of AOD use in prior 3 months, a validated measure to screen for the presence of possible alcohol and other substance use disorders. For each substance, the ASSIST assesses frequency of use, cravings, impact of use on key life domains, expressed concern from others, and failed quit attempts to derive a Specific Substance Involvement Score. If respondents indicate alcohol use, we ask the respondent’s frequency with which they had had 5 or more drinks in a row during the last 2 weeks (binge drinking), and how often the respondent drinks to get drunk. We also assess respondents’ use of alcohol and/or illicit drugs during or before condomless sex. We use the Alcohol Use Disorders Identification Test [55], a 10-item screening questionnaire with 3 questions on the amount and frequency of drinking, 3 questions on alcohol dependence, and 4 on problems caused by alcohol.

#### Biomarkers for Use of Alcohol and Other Drugs

In addition to self-reported behavioral measures of drug and alcohol use, the study will also collect biomarkers of drug and alcohol use. Participants will provide urine samples for on-site toxicology screening using an EZ split key test kit (Redwood Toxicology Laboratory, Inc.). In our prior clinical research with methamphetamine-using MSM, urine samples were obtained for toxicology testing in 98% of study visits. The on-site urine screening kits are designed to test for recent amphetamine, barbiturates, benzodiazepines, buprenorphine, cocaine, marijuana, methadone, methamphetamine, oxycodone, propoxyphene, morphine, and ecstasy. Urine toxicology screening will be used to provide information regarding recent substance use and will be conducted each study visit. Alcohol screening will be used where ethyl glucuronide (EtG) a direct metabolite of ethanol indicates that ethanol has been ingested within the last 3-4 days (80 hours). EtG will be analyzed using the 1-step EtG test dip card. Urine will be collected in a urine specimen cup and the tip of the EtG dip card will be submerged into the urine sample for 15 seconds. EtG will allow us to adjust for under-reporting of recent unhealthy drinking on participants’ surveys and will also be screened at each study visit.

#### Sexual Behaviors

Sexual behaviors will be assessed using a modified version of the Sexual Practices Assessment Schedule (SPAS) used in previous studies with YMSMTG [56] to explore different sexual acts (oral, vaginal, and anal) with different partner types. SPAS estimates the number of sexual partners and occasions across partner types, as well as the proportion of instances when condoms were not used. We also assess how frequently they report using drugs or alcohol immediately before or during sex. SPAS also ascertains YMSMTG’s HIV status disclosure practices with each partner.

#### Intervention Acceptability and Satisfaction

YMSMTG will report data on the acceptability of the intervention after completing each intervention session. We will use 2 different assessments: (1) Self-Evaluation Forms (SEF) and (2) Client Satisfaction Questionnaires (CSQ-8). The SEF is a brief 12-item questionnaire that elicits information about the experience with the intervention (ie, was the intervention interesting, was it relevant to their life, and did they learn from the intervention). The CSQ-8 will be used at the completion of the intervention to assess satisfaction with the intervention. The CSQ-8 has demonstrated high internal consistency across a large number of studies [57]. The SEF and CSQ will take approximately 10 min to complete and will be completed at the ASO on a tablet immediately after intervention delivery at visits 1 and 2.

### Statistical Analysis

Descriptive statistics of the clinical and demographic characteristics of the participants will described for all and by treatment group. These will be compared between treatment groups using *t* tests or Wilcoxon rank sum tests for continuous variables and chi-square tests for categorical variables. We will conduct primary analyses of our pooled successful engagement measure using logistic regression analyses to compare each active treatment group with the control in pairwise comparison tests at an adjusted significance level of .017 to reduce Type-I errors in our 4-arm trial. We will then conduct exploratory logistic regression analyses by sero-status. For seronegative YMSMTG, the proportion of participants who obtain at least 2 tests at least 3 months apart within 15 months will be calculated and presented with corresponding 95% exact binomial CIs. Among seropositive YMSMTG, we will examine how intervention conditions influence HIV linkage and retention in care per IOM guidelines. We will also examine for all participants the pursuit of substance use treatment services (if necessary). Hence, for seronegative participants, the outcome will be repeat HIV testing at regular intervals, and for seropositive participants, the outcome will be linkage and retention in care. We will not consider viral suppression in the regression analysis due to the short time period available to achieve suppression. However, we will present descriptive statistics on viral load and suppression across the 4 treatment arms. The regression will be run with group assignment in the model while controlling for patient, structural, and agency characteristics. Interactions between group assignment and these characteristics will be tested to explore potential moderators of treatment effect. We will repeat these analyses for STI/ATOD biomarkers conducted during the trial. Additional analyses include comparing groups in (1) the average number of tests obtained using Poisson regression and (2) time to getting tested using repeated events survival analysis.

We will test for intervention effects over time on sexual risk (eg, CAI events) and drug use (eg, reduction in ATOD use and ATOD-related consequences) outcomes. We will use the general framework of generalized linear mixed models [58-60] to model the longitudinal outcome trajectories [61-63]. Note that some of our outcomes are measured as binary, some as count, and some as continuous measures and thus need to be treated differently. Assuming a linear time trend, visit can be coded from 0 to 7, or it can be simply coded as a categorical variable representing the distinct effect of each visit compared with the baseline. The interaction coefficients are of interest here, measuring the difference in the rate of change in outcomes across the 4 treatment groups. The subject-specific random intercepts *β*_0i_ are assumed to be normally distributed with a common variance and they account for within-person correlation. We will also explore if we need a subject-specific random slope corresponding to visit in the above model. Maximum likelihood estimation will be used for fixed effect parameters. To ensure robustness, we will also apply an exchangeable working correlation structure to its corresponding generalized estimating equation model [64].

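### The factorial design is justified by sequence and dose, but for engagement the plan names and powers only comparisons of each active arm with control

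*Protocol article*

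**What the plan says.** Trial Design gives the reason for four arms: "To examine how the sequencing and dosing of interventions impacts efficacy, we randomize at baseline into a factorial RCT". Its second research question asks "what combination of services (CTR-only, CTR+SUBI, SUBI+CTR, SUBI+SUBI) has the greatest impact on engagement in HIV prevention".

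Sample Size and Power makes engagement the primary outcome. It sizes the trial for each active arm against CTR-CTR, "thus powering for 3 independent hypothesis tests", with the level "altered by the number of comparisons using a Bonferroni adjustment".

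Statistical Analysis fixes the same set. Logistic regression on the pooled engagement measure will "compare each active treatment group with the control in pairwise comparison tests at an adjusted significance level of .017".

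Three other parts of the plan compare arms in some way:
- Statistical Analysis lists additional analyses of the number of HIV tests (Poisson regression) and of time to testing (repeated events). They compare groups, but no contrast is named.
- The same section tests interactions of group with participant, structural and agency characteristics. These look for moderators. They are not the interaction of SUBI at visit 1 with SUBI at visit 2.
- The mixed models compare trajectories across all four groups, but for sexual risk and drug use only.

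**The concern.** The four arms are a 2×2 layout: SUBI at visit 1 (yes or no) by SUBI at visit 2 (yes or no). Sequence is the contrast SUBI+CTR against CTR+SUBI. Dose is SUBI+SUBI against each arm with one SUBI session. Neither is stated for the pooled engagement measure.

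Three tests against a common control show whether each active arm beats CTR-only. They do not test whether one active arm beats another. If no other comparison is reported, the natural shortcut is to call the arm that reaches significance the best and the one that misses it inferior. A difference in significance is not a significant difference, so a service organization could prefer one sequence, or pay for a second SUBI session, on the strength of noise.

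**Working it through.** **Inputs.** From the protocol: 1:1:1:1 allocation; two-sided .05 divided by 3 = .0167 (printed as .02 in Sample Size and Power and .017 in Statistical Analysis); 80% power; 500 participants for a 20-point difference and 228 for 30 points; 600 enrolled; 20% loss. The control rate is not stated. I assume 30%.

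**1. The plan's own figures.** Per-arm size for a two-sample test of proportions with pooled variance under the null and no continuity correction:

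n = [z(1−α/2)·√(2p̄(1−p̄)) + z(.80)·√(p₁(1−p₁)+p₂(1−p₂))]² / (p₂−p₁)², with z values 2.394 and 0.842.

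- 30% vs 50%: (2.394×0.693 + 0.842×0.678)² / 0.04 = 124.3, so 125 per arm and 4×125 = 500.
- 30% vs 60%: (2.394×0.704 + 0.842×0.671)² / 0.09 = 56.2, so 57 per arm and 4×57 = 228.

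Both stated totals reproduce exactly. For control rates of 20% to 60% the 20-point total runs from 436 to 520. The trial was sized for the three control comparisons and nothing else.

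**2. Evaluable numbers.** 600×0.8 = 480, or 120 per arm. Power for 30% vs 50% at .0167 is then 78%.

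**3. How often equal arms look unequal.** Let control be 30% and every active arm 50%, with 120 per arm and the pooled z-test at .0167. For a given control count, let P be the chance that an active arm is significant. Averaging over the control count:
- two arms, exactly one significant: mean of 2P(1−P) = 23.7%;
- three arms, verdicts not all the same: mean of 1−P³−(1−P)³ = 35.6%.

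The shared control makes verdicts agree more often than they would if independent (2×0.78×0.22 = 34% for two arms), and disagreement is still frequent.

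**4. What direct contrasts can deliver.** 95% half-width for a difference between two active arms, both near 60%: 1.96×√(2×0.6×0.4/120) = 12.4 points. Power for a true 10-point difference (45% vs 55%, 120 per arm) is about 34% at unadjusted .05, and about 14% if all six pairs are tested at .05/6.

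**5. Factorial margins.** Each margin compares 240 with 240. The half-width is 1.96×√(2×0.6×0.4/240) = 8.8 points. Under the scenario in step 3, however, the visit-1 margin is (50+50)/2 = 50% against (30+50)/2 = 40%, only 10 points. Its power is about 60% at .05, or 48% at .025 for two main effects, against 78% for each planned pairwise test.

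**The case against.** The best defence is that the article condenses a fuller document and that little is truly missing. The logistic model contains group assignment, so it yields an estimate for every arm and any contrast between arms, and those estimates can be ranked. The Poisson and time-to-testing analyses already compare groups on repeat testing. Secondary contrasts are commonly left to the analysis plan. Contrasts between active arms would also be too imprecise to settle much.

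Most of this stands as a limit on the point. It does not remove it: the article itself states the contrasts, their number and their level, sizes the trial on them, and does not match them to the question that justified four arms. Low precision is a reason to show the intervals.

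Four stronger readings are tempting and are not supported:
- *The first research question is unanswered too.* The control comparisons address its engagement part, and the mixed models address sexual and substance-related risk.
- *The trial cannot identify the best arm at all.* That holds only for formal inference from the stated tests. Point estimates will be available.
- *The investigators will rank arms by significance.* Nothing says so. The 24% and 36% show what that shortcut would cost, not what is planned.
- *A main-effects analysis would be more powerful in general.* Step 5 shows the reverse when one SUBI session works as well as two. Setting margins at .05 beside pairwise tests at .0167 would also credit the design with a gain that comes partly from dropping the multiplicity adjustment.

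**Conclusion.** The concern holds for the second research question and for the sequencing and dosing purpose, on the pooled engagement measure. The stated analysis and power cover three active-versus-control tests, and no stated contrast bears on which active arm "has the greatest impact on engagement in HIV prevention".

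The size of the problem is the risk in the shortcut: about 24% opposite verdicts for two equally effective arms and about 36% disagreement among three. These figures assume a 30% control rate, a 20-point benefit in each active arm and 120 evaluable per arm. The mismatch itself does not depend on these assumptions. It does not undermine the three primary comparisons.

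**What to change.** Keep the three control comparisons, their significance level and the sample size as primary. Then do one of the following:

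- Prespecify, as secondary estimates from the same logistic model, (a) SUBI+CTR vs CTR+SUBI and (b) SUBI+SUBI vs each single-SUBI arm, with 95% confidence intervals. State that any claim about the best sequence or dose rests on these contrasts and not on which arms reach significance against control.
- Or restate the second research question as descriptive.

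Visit-1 and visit-2 main effects with their interaction may be added as supportive estimates, with the simple effects beside them. They are a more precise summary only when the interaction is small, and they lose power if one session does as much as two.

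The cost is wording: no new data and no change to the primary analysis. The Results section reports 142 participants randomized by February 2018 with enrollment continuing, so as of that report the contrasts could still be prespecified. The downside is that intervals between active arms will be about ±12 points, so these contrasts should be labelled as estimates and not as powered tests.
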